# Expanded nursing roles to promote person-centred care for people with cognitive impairment in acute care (ENROLE-acute): study protocol for a controlled clinical trial, process and economic evaluation

**DOI:** 10.1186/s12877-023-04560-3

**Published:** 2023-12-14

**Keywords:** Person-centred care, People with cognitive impairment, Expanded nursing roles, Advanced Practice Nursing, Hospital, Complex intervention, Study protocol, Controlled clinical trial, Process evaluation, Economic evaluation

## Abstract

**Background:**

For people with cognitive impairment, hospitalisation is challenging and associated with adverse events as well as negative outcomes resulting in a prolonged hospital stay. Person-centred care can improve the quality of care and the experience of people with cognitive impairment during hospitalisation. However, current care processes in German hospitals are rarely person-centred. To enable successful implementation of person-centred care on hospital wards, change agents within the interprofessional team are key. The aim of this study is to test the feasibility and initial effects of a newly developed complex person-centred care intervention for people with cognitive impairment provided by expanded practice nurses in acute care.

**Methods:**

We will conduct an exploratory non-randomised controlled clinical trial with accompanying process and cost evaluation with three intervention and three control wards at one university hospital. The person-centred care intervention consists of 14 components reflecting the activities of expanded practice nurses within the interprofessional team on the intervention wards. The intervention will be implemented over a six-month period and compared with optimised care on the control wards. We will include people aged 65 years and older with existing cognitive impairment and/or at risk of delirium. The estimated sample size is 720 participants. The primary outcome is length of hospital stay. Secondary outcomes include prevalence of delirium, prevalence of agitation, sleep quality, and person-centred care. We will collect patient level data at six time points (t_1_ admission, t_2_ day 3, t_3_ day 7, t_4_ day 14, t_5_ discharge, t_6_ 30 days after discharge). For secondary outcomes at staff level, we will collect data before and after the intervention period. The process evaluation will examine degree and quality of implementation, mechanisms of change, and the context of the complex intervention. The economic evaluation will focus on costs from the hospital’s perspective.

**Discussion:**

The ENROLE-acute study will provide insights into the effectiveness and underlying processes of a person-centred care intervention for people with cognitive impairment provided by expanded practice nurses on acute hospitals wards. Results may contribute to intervention refinement and evidence-based decision making.

**Trial registration:**

Current controlled trials: ISRCTN81391868. Date of registration: 12/06/2023. URL: https://doi.org/10.1186/ISRCTN81391868

**Supplementary Information:**

The online version contains supplementary material available at 10.1186/s12877-023-04560-3.

## Background

In 2021, almost half of patients in German hospitals were 65 years and older [1]. Older age is associated with cognitive impairment, with a prevalence among elderly hospital patients ranging from 40 to 67.5% [2, 3]. This mainly includes people living with dementia, mild cognitive impairment, and with delirium [3].

Hospitalisation of people with cognitive impairment is associated with several challenges. One challenge is a frequently missing formal diagnosis of cognitive impairment [2, 3], resulting in care that is not tailored to the needs of this vulnerable patient group. An integrative review on hospital outcomes [4] found, that people with cognitive impairment encounter a hospital environment focussed on acute illness rather than their individual needs, as shown by avoidable bed moves, inadequate pain management, inappropriate catheterisation, and poor communication and relationship building with healthcare professionals. Negative experiences are common, frequently leading to feelings of fear and an increase in behavioural and psychological symptoms. In addition, people with cognitive impairment are more likely to encounter a range of related adverse events such as the incidence of delirium, urinary tract infections, pneumonia, pressure ulcers, adverse drug reactions, and falls, that may lead to prolonged hospital stays and increased mortality [4]. Healthcare professionals struggle with the discrepancy between desirable hospital care and the current reality of care for people with cognitive impairment, resulting in distress and frustration, uncertainty in dealing with changed behaviour, conflicting priorities, and the inability to meet individual needs [5].

A key to improve hospital care for people with cognitive impairment is the concept of person-centred care (PCC), which has been recommended in guidelines [6, 7] and by representative organisations [8]. Person-centredness has been applied to different target groups such as people living with dementia [9], different healthcare professionals such as nurses [10], and different care contexts such as hospitals [11]. Despite the widespread use of PCC, there is no consensus on how it is operationalised conceptually. According to a recent scoping review [12], the most common of nine identified dimensions of person-centredness are “perception of the individual as a unique person”, “sharing of responsibility between person and practitioner”, and “formation of a therapeutic relationship". However, the literature indicates a gap between the theoretical concept and practical implementation of PCC in the hospital setting [13]. Reported barriers to provide PCC include lack of knowledge, understanding and training of healthcare professionals [5, 14], ward and institutional cultures, and inappropriate physical environment [5]. To promote PCC in hospitals, change is needed at both institutional and ward levels. Here, leadership of key personnel plays a crucial role, as staff training is not sufficient to implement PCC successfully [15–17]. At ward level, so-called change agents with clinical expertise can support staff awareness and initiate change processes in care [17]. This role of a clinical leader reflects one core competence of an Advanced Practice Nurse (APN) [18], a specialised nurse with a master’s degree, possessing expert knowledge, complex decision-making skills, and clinical competencies [19]. APN interventions for older people have shown positive outcomes in primary and long-term care. Evidence for the acute setting shows mixed results [20, 21].

As Germany is at the beginning of establishing APN, Expanded Practice Nurses (EPN) at bachelor’s level are deployed to facilitate the transition to Advanced Practice Nursing [22, 23]. Expanded nursing roles for PCC for people with cognitive impairment in hospitals are rarely described in the literature [24, 25].

The development and implementation of an EPN role is complex as various components and their interactions need to be taken into account. To comprehensively investigate complex interventions, the guidance of the British Medical Research Council (MRC) recommends the evaluation of effects, while considering underlying processes and influencing factors as well as costs [26].

In the ENROLE-acute (Expanded Nursing ROLEs for person-centred care for people with cognitive impairment in ACUTE care) project, we are developing, implementing, and evaluating a complex PCC intervention for people with cognitive impairment, delivered by EPN on peripheral wards in one acute hospital. We hypothesise that by introducing PCC, the individual needs of people with cognitive impairment will be addressed in a timely manner and thus adverse events will be reduced or avoided, leading to a reduction in the length of hospital stay.

## Objectives

This study aims to test the feasibility and clinical effectiveness of the newly developed PCC intervention. Therefore, our objectives are to assess (a) initial effects, (b) the degree and quality of implementation, mechanisms of change and contextual factors, and (c) potential cost savings of the intervention.

## Methods / Design

### Overall study design

The ENROLE-acute project follows the first and second stage of the MRC guidance [26] for complex interventions, with this study protocol addressing the feasibility stage. Protocol development adheres to the SPIRIT checklist [27] (see Additional file 1).

To examine initial effects of the ENROLE-acute intervention, we will conduct an exploratory non-randomised controlled clinical trial (CCT), comparing the PCC intervention and optimised care as control intervention. The CCT will be accompanied by an embedded mixed-methods process evaluation to explore how and under what circumstances outcomes are achieved. In addition, we will conduct a health economic evaluation. Figure 1 summarises the overall study design.

**Fig. 1 Fig1:**
[figure not shown]
Participant timeline

### Setting

We will conduct the study in one university hospital in the western part of Germany. The hospital has about 1,500 beds, with inpatient care provided to 57,900 patients in 2022. According to internal hospital controlling, about 1,500 people with diagnosed cognitive impairment were treated as inpatients in the same year.

The hospital has about 12,000 employees [28]. In recent years, first EPN have been introduced. At present, there are 36 nurses working in expanded roles in wound management, oncology, psychiatry, obstetrics and gynecology, surgery, and cardiology [29, 30].

### Intervention

In the first phase of the ENROLE-acute project, we comprehensively developed the complex intervention based on two systematic reviews, two surveys [31], one qualitative interview study, and two workshops with relevant stakeholders from clinical practice, research, and representative organisations of people with cognitive impairment. We will publish details of intervention development elsewhere.

The complex intervention aims to foster PCC for people with cognitive impairment through EPN acting as change agents (see Fig. 2). We defined 14 components reflecting EPN’s role in collaboration with the interprofessional team. The model includes core components that are mandatory (no. 1–12) and peripheral components that are adaptable (no. 13–14) [32]. We differentiate between patient-related and system-related components. Patient-related components are aimed at individual patients and include screening and expanded nursing assessment at patient admission (no. 1–2); planning, conducting, and evaluating PCC interventions in collaboration with registered nurses (no. 3, 4 and 9); and further EPN interventions including case conferences on discharge planning, coaching relatives, and conducting and initiating consultations (no. 5–8). System-related components include EPN interventions at the organisational level, e.g., training interventions for staff, monitoring of change processes, promoting hospital-wide collaboration, conceptual work, and nursing research (no. 10–14).

**Fig. 2 Fig2:**
[figure not shown]
Intervention components

Each intervention ward receives two EPN, qualified at level six of the European Qualifications Framework (bachelor’s degree or equivalent further education) [33]. EPN are integrated into the ward's work schedule and have one day each every two weeks for additional activities.

We developed different implementation strategies to prepare the field. EPN received a 200-h training regarding fundamentals of caring for people with cognitive impairment, principles of PCC, and Advanced Practice Nursing in six modules. In addition, EPN gained knowledge of established expanded nursing models in other hospitals during a 10-day internship. During the intervention period, we accompany the EPN fortnightly in two-hour coaching sessions for reflection and implementation support. We also train the interprofessional team at the beginning of the intervention phase on PCC principles and Advanced Practice Nursing during a one-hour kick-off meeting and through written information.

Team members of control wards provide optimised care with knowledge acquired through a one-time half-hour session and written information on PCC.

### Evaluation of effects

#### Participants

For details on the inclusion criteria of all participants, please see Additional file 2.

##### Patient level

We defined the following inclusion criteria for potential participants: (1) age of 65 years and older, (2) sufficient knowledge of German language, (3) hospital stay of unclear duration or over 48 h, (4) ability to consent or existence of a legal representative, and (5) present cognitive impairment (e.g., diagnosis of dementia) or risk for cognitive impairment (e.g., risk for delirium) according to predefined criteria.

We will recruit potential participants on six days a week over a time period of six months. Contact persons of the respective wards will inform eligible people with cognitive impairment and, if necessary, their representatives about the study and ask for consent to be approached by the research team for obtaining informed consent.

##### Staff level

Members of the interprofessional team are registered nurses (European Qualifications Framework level 4), nursing assistants, and physicians of all participating wards. We exclude therapists as well as service and administrative personnel as they do not form the core of the interprofessional team on a ward. We will recruit members of the interprofessional team during kick-off meetings and via superiors.

##### Cluster level

We will purposefully select six peripheral wards with a prevalence of at least 30 people with cognitive impairment per month according to data from hospital controlling. We will exclude intensive care, intermediate care, psychiatric, palliative, and paediatric wards. Based on the recommendation of nursing management, we will identify eligible wards and recruit them through individual information meetings with ward managers.

#### Outcomes, data collection and management

For an overview of primary and secondary outcomes, instruments used, data collection time points, and data sources, please see Table 1.

**Table 1 Tab1:** Overview of the evaluation of effects

Variable	Instrument	Description	Source	Time points^a^	Type of variable
**PEOPLE WITH COGNITIVE IMPAIRMENT**					
Length of hospital stay	Single item	Number of days people with cognitive impairment stayed in hospital during a single admission event [34]	Patient records	t_5_	Primary outcome
Prevalence of delirium	Confusion Assessment Method – short form (CAM)	The Confusion Assessment Method consists of 4 items on (1) acute onset and/or fluctuating course, (2) inattention, (3) disorganised thinking, and (4) altered level of consciousness. Delirium is indicated sensitively if item (1) and (2), and either (3) or (4) are scored positive [35–37]	Rating by research team	t_1_, t_2_, t_3_, t_4_, t_5_	Secondary outcome
Severity of delirium	Confusion Assessment Method – Severity (CAM-S)	Delirium severity is measured using the Confusion Assessment Method by rating the items in terms of severity (0 = absent, 1 = mild, 2 = marked). The item (1) acute onset and/or fluctuating course is only rated as 0 = absent or 1 = present. Overall, the scale ranges from 0—7 points, with higher values indicating a more severe degree [38]	Rating by research team	t_1_, t_2_, t_3_, t_4_, t_5_	Secondary outcome
Delirium subtype	Delirium Motor Subtype Scale (DMSS)	The Delirium Motor Subtype Scale consists of two subscales on hyperactive (4 items) and hypoactive (7 items) subtype, classifying four different motor subtypes: hypoactive, hyperactive, mixed or no motor subtype. Each item is scored dichotomously (present or absent) over the past 24 h. Hyperactive delirium is positive, when two items on the hyperactive subscale are present. Hypoactive delirium is positive, when either “decreased amount of activity” or “decreased speed of actions” in combination with at least one other item is present. Mixed type is positive, when both hyper- and hypoactive delirium was positive within the last 24 h [39, 40]	Rating by registered nurses	t_1_, t_2_, t_3_, t_4_, t_5_	Secondary outcome
Prevalence of pain	Numeric Rating Scale (NRS)	The Numeric Rating Scale is a 11-point scale ranging from 0 (no pain) to 10 (worst possible pain) [41]. A value ≥ 1 indicates pain	Self-rating by people with cognitive impairment	t_1_, t_2_, t_3_, t_4_, t_5_	Secondary outcome
	Pain Assessment in Advanced Dementia (PAINAD-G)	If self-assessment is not possible with NRS, the Pain Assessment in Advanced Dementia (PAINAD-G) will be used. PAINAD-G consists of five items (breathing, negative vocalisation, facial expressions, body language, consolability) resulting in a score from 0 (no pain) to 10 (worst possible pain) [42, 43]. A score > 2 is defined as an indicator for pain [44]	Rating by research team	t_1_, t_2_, t_3_, t_4_, t_5_	Secondary outcome
Prevalence of unrecognised pain	NRS / PAINAD-G	Unrecognised pain is defined by identified pain by the research team and, at the same time, no documentation of pain or administration of medication on demand in patient records	Discrepancy between rating by research team and patient records	t_1_, t_2_, t_3_, t_4_, t_5_	Secondary outcome
Prevalence of agitation	Cohen Mansfield Agitation Inventory (CMAI, hospital version)	The hospital version of the Cohen Mansfield Agitation Inventory consists of 9 items on a 7-point scale measuring frequency of agitated behaviour (including two subscales on aggressive and non-aggressive behaviour) with a time reference of one week. A score between 9 and 63 can be achieved, with higher scores reflecting a higher level of agitation [45, 46]	Retrospective rating by registered nurses	t_3_, t_4_, t_5_	Secondary outcome
Anxiety, stress, and depression	Depression Anxiety Stress Scales (DASS) – short form	The Depression Anxiety Stress Scales consist of 21 items, which are divided into 7 items each for the constructs depression, anxiety and stress. On a 4-point scale, the extent is rated from 0 = not at all true to 4 = very true or true most of the time. The time reference is a period of one week. A sum score is calculated for each subscale, with higher values indicating a higher degree of the negative emotional state. A score of 10 for depression and stress, as well as a score of 6 for anxiety can be assumed to indicate an increased expression of these characteristics [47]	Self-rating by people with cognitive impairment	t_1,_ t_3_, t_4_, t_5_	Secondary outcome
Quality of sleep	Richards-Campbell-Sleep-Questionnaire (RCSQ)	The Richards-Campbell-Sleep-Questionnaire consists of 5 items on sleep depth, falling asleep, being awake, falling asleep again and sleep quality. The evaluation of the individual items refers to the previous night and is done using a visual analogue scale, with 0 mm representing the worst sleep and 100 mm the best sleep [48, 49]	Self-rating by people with cognitive impairment	t_2_, t_3_, t_4_, t_5_	Secondary outcome
	Outcome-oriented nursing assessment AcuteCare (epa-AC ©^b^)	Sleep problems are described in epa-AC using two items, the presence of falling asleep and staying asleep as well as a disturbed sleep–wake rhythm [50]	Patient records	t_2_, t_3_, t_4_, t_5_	Secondary outcome
Quality of life	Bath Assessment of Subjective Quality of Life in Dementia (BASQID)	The Bath Assessment of Subjective Quality of Life in Dementia includes 14 items divided into two subscales on life satisfaction and feeling of a positive quality of life. Both subscales are used with a 5-point Likert scale ranging from 0 = not at all satisfied or not at all to 4 = extremely satisfied or very satisfied. Overall, the scale results in a transformed score of 0—100 points, with higher values indicating a higher quality of life. Three additional questions provide a comprehensive assessment of quality of life, health, and memory performance and are evaluated separately [51, 52]	Self-rating by people with cognitive impairment	t_5_	Secondary outcome
	QUALIDEM	The QUALIDEM uses 37 items to measure the quality of life of people with dementia, with a selection of 18 items being used for people with severe dementia. The 18-item version addresses the domains care relationship, positive affect, negative affect, restless and tense behaviour, social relationships, and social isolation. Responses are made using a 7-point Likert scale that asks for frequency. Although an analysis within domains is recommended, a total score of 0—168 points can also be calculated, with higher values representing a higher quality of life [53, 54]	Retrospective rating by registered nurses	t_5_	Secondary outcome
Person-centred care	Individualised Care Scale (ICS)	The Individualised Care Scale consists of 17 items measuring the perspective of people with cognitive impairment on implementation of individualised care during hospitalisation. Items are rated with a 5-point Likert scale ranging from 1 = strongly disagree to 5 = strongly agree. A general score is calculated as mean value between 1 and 5, with higher values indicating more individualised care [55, 56]	Self-rating by people with cognitive impairment	t_5_	Secondary outcome
Falls	Single items	Number of falls documented	Patient records	t_5_	Secondary outcome (safety outcome)
Physical restraints	Single items	Occurrence of the use of physical restraints	Retrospective rating by registered nurses	t_2_, t_3_, t_4_, t_5_	Secondary outcome (safety outcome)
Prescription of antipsychotics	Predefined list	Newly prescribed antipsychotic medication during hospitalisation	Patient records	t_5_	Secondary outcome (safety outcome)
Mortality	Single items	People with cognitive impairment that died during data collection	Patient records	t_6_	Secondary outcome (safety outcome)
Stability of care arrangements	Single items	• Number of readmissions within 30 days • Perceived stability of care arrangement	Telephone interview with people with cognitive impairment and/or their relatives	t_6_	Secondary outcome (safety outcome)
Sociodemographic variables	Single items	• Age in years • Gender: Male, female, or divers • Care dependency levels ranging from 1 to 5 • Care situation before admission	Patient records	t_1_	Control variable
Admission diagnosis	Single items	Admission diagnosis as documented	Patient records	t_5_	Control variable
Type of admission	Single items	Emergency or planned admission	Patient records	t_1_	Control variable
Previous hospital admissions	Single items	Number of hospital admissions within the last seven days	People with cognitive impairment and/or their relatives	t_1_	Control variable
Admission diagnosis-related (diagnosis related groups) length of hospital stay	Single items	Mean stated length of stay of the patient's diagnosis-related group	Patient records	t_5_	Control variable
Or Ward-related length of hospital stay		Minimum length of stay of special wards, e.g., based on rehabilitation programmes	Ward managers	t_0_	
Type of discharge	Single items	Discharge home, transfer	Patient records	t_5_	Control variable

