**STAFF**					
Distress associated with difficult behaviour for people with cognitive impairment	Residents’ Challenging Behaviour related Distress Index	The Residents’ Challenging Behaviour related Distress Index includes 10 items that address altered behaviour such as hallucinations, instability, anxiety, depression, apathy, euphoria, limited communication skills, disinhibition, aggression, and impaired motor skills. All items are rated in terms of the degree of distress 1 = does not stress me at all, 2 = stresses me somewhat, and 3 = stresses me a lot. The score ranges from 0—100 points, with a higher score indicating higher distress [60]	Self-rating by staff	t_0_, t_7_	Secondary outcome
Person-centred care	Person-Centred Practice Inventory – Staff (PCPI-S)	The Person-Centred Practice Inventory—Staff includes 59 items covering 17 different constructs of person-centredness with respect to 3 domains: prerequisites, care environment, and person-centred processes. The items are measured on a 5-point Likert scale from 0 = strongly disagree to 4 = strongly agree. Overall, the scale shows a sum score of 0—100, with higher scores representing greater agreement with person-centredness [61, 62]	Self-rating by staff	t_0_, t_7_	Secondary outcome
Sociodemografic variables	Single items	• Age in years • Gender	Self-rating by staff	t_0_, t_7_	Secondary outcome

^a^t_0_ = before implementation of intervention; t_1_ = admission; t_2_ = day 3 of hospital stay; t_3_ = day 7 of hospital stay; t_4_ = day 14 of hospital stay; t_5_ = discharge from the ward; t_6_ = 30 days after discharge; t_7_ = 6 months after baseline

^b^With Outcome-oriented nursing assessment AcuteCare (epa-AC ©) the patient's abilities and impairments are assessed daily by registered nurses using the four-level epa point system and recorded in electronic form [50]

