#### Data analysis

Statistical analysis is according to intention-to-treat (no exclusions). We will evaluate the primary outcome length of hospital stay by the stratified log-rank test (death is censored). Nota bene, the stratified log-rank test has very similar characteristics as the stratified van-Elteren rank-sum test and is available in many (statistical) software packages. We will use a propensity score approach (PSA) to balance individual characteristics between participants in intervention and control groups. In the multivariable logistic regression for PSA, we will use the independent variables age, gender, severity of cognitive impairment, Charlson Comorbidity Index, admission type, expected admission diagnosis-related or ward-related length of stay, and hospitalisations during the last 7 days [66, 67] as these variables are likely to be associated with outcome. Moreover, we will carefully monitor mortality in both arms, although we do not expect any difference. We will evaluate secondary outcome measures by (generalised) mixed models for repeated measures over time. If feasible, we will take outcome measures (particularly those reported by people with cognitive impairment) over the course of hospital stay. Thus, we may need to evaluate the outcome trajectories by random coefficient models. We will categorise and compare safety outcomes by frequency, relatedness, seriousness, and severity. Moreover, we will summarise variables by mean, standard deviation, and percentiles (0, 25, 50, 75, and 100) respectively by absolute and relative frequencies (percentage). Due to the small number of clusters, we will at least account for them in a fixed effect analysis. Though we will attempt to estimate corresponding random effects (e.g., to derive intraclass correlation), this seems prone to bias.

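### The primary log-rank test names no entry time, so event-free days before enrolment count as time at risk; if enrolment lag differs by arm, the faster-enrolling arm appears to have shorter stays

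*Protocol article*

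**What the plan says.** Table 1 of the protocol article defines the primary outcome as "Number of days people with cognitive impairment stayed in hospital during a single admission event", taken from patient records at t5. No time zero is stated. Footnote a to Table 1 labels t1 as admission without saying whether to the hospital or the ward, counts later visits in hospital days ("t_2_ = day 3 of hospital stay"), and defines t5 as discharge from the ward. The natural reading is a clock that starts at hospital admission, but the end point could be read as leaving either the ward or the hospital.

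Entry to the study is described under Participants, Patient level. "Contact persons of the respective wards will inform eligible people with cognitive impairment" and, where needed, their representatives, and "ask for consent to be approached by the research team for obtaining informed consent". Recruitment runs six days a week. Eligibility requires a "hospital stay of unclear duration or over 48 h". Under Cluster level, "We will exclude intensive care, intermediate care, psychiatric, palliative, and paediatric wards", so days spent on such units before transfer fall outside the study wards. Under Assignment of intervention, the patient's arm follows from the ward, and ward managers decided whether to take part in the intervention.

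For the analysis: "We will evaluate the primary outcome length of hospital stay by the stratified log-rank test (death is censored"). The Data analysis section names no entry time, and neither enrolment lag nor days before the study ward is among the listed propensity-score variables.

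**The concern.** Every participant must still have been in hospital at enrolment. Someone discharged on day 2 who would have consented on day 3 never enters the data, and analysing all enrolled patients by intention to treat cannot bring that person back. A log-rank test that puts everyone at risk from admission treats the admission-to-enrolment interval as follow-up in which discharge could have been seen. This is left truncation without adjustment.

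Mean stay among patients who stay beyond day d never falls as d grows. The arm that enrols later therefore shows the longer observed stay even if care has no effect. A difference in lag is plausible for three reasons: screening and expanded assessment at admission are mandatory components on intervention wards (Intervention section), wards chose their arm, and ward staff and data collectors are not blinded.

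At stake is the one claim the trial is sized for. The Sample size section says that the trial is powered to show the direction of effect only, so a modest systematic shift bears directly on that result.

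**Working it through.** **The plan's own figure.** Inputs from Sample size: difference 3 days, SDs 18 and 16, ICC 0.05, 3 wards of 120 per arm, one-sided level 50%.

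- Design effect = 1 + 119 × 0.05 = 6.95
- SE = √[(18² + 16²) × 6.95 / 360] = 3.346 days
- Power = Φ(3 / 3.346 − 0) = Φ(0.897) = 81.5%, as stated

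On the same scale with no true effect, a spurious shift of 1, 2 or 3 days raises the chance of a result in the favoured direction from 50% to 62%, 72% or 81.5%.

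**How large a shift can unequal lag produce?** The article gives neither mean stay nor enrolment lag, so both are assumed. For log-normal stays with mean M and SD s:

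- σ² = ln(1 + s²/M²), μ = ln M − σ²/2
- E[stay | stay > d] = M × Φ((μ + σ² − ln d)/σ) / Φ((μ − ln d)/σ)

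For M = 14 and s = 16: σ² = 0.836, σ = 0.914, μ = 2.221.

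| Entry day d | Share discharged before d | Mean stay if enrolled |
|---|---|---|
| 2 | 1 − 0.9527 = 4.7% | 14 × 0.9951/0.9527 = 14.62 |
| 3 | 1 − 0.8903 = 11.0% | 14 × 0.9839/0.8903 = 15.47 |
| 4 | 1 − 0.8195 = 18.1% | 14 × 0.9662/0.8195 = 16.51 |

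The spurious difference is 0.8 days (day 2 versus 3) or 1.9 days (day 2 versus 4). With mean/SD 12/10 it is 0.4 or 1.1 days; with 16/17, 0.6 or 1.5 days. Over means of 10 to 20, SDs of 10 to 17 and lags of 1 v 2, 1 v 3, 2 v 3 and 2 v 4 days, it runs from 0.0 to 3.4 days.

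**Effect on the log-rank test.** Simulation with no treatment effect, 3 wards × 120 per arm, mean 14 and SD 16, and a ward effect with ICC 0.05 on the log scale. Deaths, strata and propensity adjustment are left out.

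| Enrolment lag | Trials favouring the faster arm, clock from admission | With delayed entry |
|---|---|---|
| Fixed, day 2 v 3 | about 65% | about 50% |
| Fixed, day 2 v 4 | 80 to 83% across repeated simulations | about 50% |
| Random, means 1 v 2 days, all stays over 48 h | about 56 to 59% | about 50% |

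Without any ward effect the first two rows would be 81 to 84% and 97 to 98%. Those figures ignore the protocol's own ICC and should not be used.

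**Does counting from enrolment do as well?** Not quite. With random lags averaging 1 v 3 days, mean stay 14 and SD 17, the null hazard ratio for discharge in the faster arm is 1.09 from admission, 0.99 with delayed entry and 0.98 counted from enrolment. Across the 1 v 3 day scenarios, counting from enrolment ranged from 0.93 to 1.02. In the simulated trials it favoured the faster arm in about 41 to 47%, a smaller bias in the opposite direction.

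**The case against.** Five points can be made for the plan.

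1. **Time zero is inferred.** The article does not write down a start. That is correct, and the ambiguity is part of the point.
2. **No difference in lag is documented.** The same recruitment route, ward contact persons and then the research team, is described for all wards, and nothing says that the expanded practice nurses' screening feeds recruitment. This stands. A reader might infer that the bias must favour the intervention; the article supports only that it favours whichever arm enrols faster.
3. **The design already limits the problem.** The 48-hour criterion removes many very short stays, and research-team ratings at t1 imply enrolment near admission. This reduces the bias. It does not remove it, because stays of unclear duration are eligible, consent may need a representative, and recruitment does not run every day.
4. **Days before the study ward are not in themselves an error.** A reader might treat them as one. Total hospital stay is a legitimate quantity and is compared in the cost-consequence analysis. Such days add noise, and they bias the comparison only if transfers differ by arm, which the article does not show. Admission type and expected stay in the propensity score adjust for part of this.
5. **This is detail for a fuller document, and the Discussion already concedes a high risk of selection bias.** Recording of dates could well be specified elsewhere. But the article itself fixes the outcome, the test and the covariates, and as fixed they leave the entry time unprotected. The Discussion's remedy is to consider baseline differences between groups in the analysis; that does not correct for patients absent because they left before consent.

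**Conclusion.** The point holds in conditional form. The outcome and test, as written, treat time before enrolment as time at risk although no discharge can be observed in it. If enrolment lag differs by arm, the faster-enrolling arm will appear to have shorter stays.

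Under log-normal stays with mean 14 and SD 16 days, a one- or two-day difference in fixed entry (day 2 v 3, day 2 v 4) gives 0.8 or 1.9 spurious days against the planned 3. In the two-day case, a trial with no effect shows the favoured direction about as often as the 81.5% planned for a true effect. Under milder assumptions (all stays over 48 hours, random lags averaging 1 v 2 days) the share is 56 to 59%. If all stays exceed 48 hours and both arms enrol within 48 hours, the problem is near zero.

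These sizes rest on an assumed distribution of stays and assumed lags. The article neither shows unequal lag nor establishes that any bias would favour the intervention.

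**What to change.** - State time zero explicitly, and say whether the end point is discharge from the hospital or from the ward, so that the Table 1 definition and the t5 label agree.
- Record the dates of hospital admission, arrival on the study ward and consent for every participant.
- Run the primary log-rank or Cox analysis on the days-since-admission scale with delayed entry: each patient joins the risk set at enrolment.
- Report enrolment lag and days before the study ward by arm, so that readers can judge whether the condition for bias was met.
- Keep total hospital stay as a descriptive figure and for the economic analysis.
- Do not substitute days from t1 as though it were equivalent; it does not fully remove the bias when the discharge hazard changes over the stay.

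The cost is a few sentences and three dates per patient. The analysis has slightly fewer patient-days at risk.
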